**Figure 1 F1:**
[figure not shown]
**Anticipated statistical power estimations in Trials I and II**. The anticipated power in the trials on the x-axis as a function of the sample size of the trials on the y-axis based on α = 0.05 and an anticipated hazard ratio of 0.65 and 6 month median time from randomisation to re-admission to hospital in the control group, 48 month inclusion period, and at least a 12 month follow up of all patients.

The assumption of time to re-hospitalisation was based on national hospital data showing that half of all patients hospitalised with a diagnosis of depression or mania/bipolar disorder are re-hospitalised within a few months [85]. The assumption that the proportion of re-admission would be 35% decreased in the intervention group compared with the intervention group was based on findings of the effect of psychoeducation in bipolar disorder [86] and further on presumptions of positive effects of the early contact to patients during the vulnerable period following hospital discharge (less than two weeks) and a low drop out in the intervention group as experienced during the pilot phase of the trials.

### Statistical analyses

Separate statistical analyses will be made for patients with bipolar disorder and patients with unipolar disorder. The statistical analyses will be made as 'intention-to-treat' analyses. Regarding the primary outcome, time to the first re-hospitalisation will be estimated in Kaplan-Meier plots. The difference in cumulated prevalence of re-hospitalisation in the intervention and in the control group will be tested in log-rank tests. The absolute and relative hazard risk reductions and the corresponding 95% confidence intervals will be calculated. In addition, hazard ratios adjusted for age, sex, psychiatric centre, and number of previous admissions will be calculated in Cox' regression models.

Analyses comparing participants and eligible non-participants in the trials will be carried out using data from the Danish Central Psychiatric Register to identify any difference between these groups regarding sex, age, primary diagnosis, diagnoses of comorbidities, and number of previous admissions to psychiatric hospitals.

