## Background and objective

### Background

Affective disorders are associated with a high risk of relapse and the risk of relapse increases as the number of previous episodes increases [1,2]. Many patients do not recover to previous psychosocial function [3,4]. A proportion of patients present with cognitive impairment also during the remitted phase [5-7], and the risk of developing dementia seems increased in the long run [8,9]. It is well documented from randomised clinical trials that the risk of a new episode in bipolar disorder can be reduced significantly by treatment with lithium or other mood stabilizers [10]. In unipolar disorder continued treatment with antidepressants significantly reduces the risk of relapse [11]. Further, the prophylactic effect of medical treatment may be enhanced by psychoeducation or cognitive behavioural therapy in bipolar disorder [12-17] and by cognitive behavioural therapy in unipolar disorder [18-20]. However, results from naturalistic follow up studies suggest that the progressive development of the diseases is not prevented in clinical practice with the present treatments [21-23]. Part of the explanation may be decreased adherence with mood stabilizers and antidepressants, [24-29] but another explanations may be delayed intervention - pharmacologically and psychologically. Results from a number of studies comparing specialist first episode anti-psychosis programs versus standard treatment have shown that there are positive effects of early and sustained intervention following the first psychotic episode [30]. Within affective disorders, a number of studies have investigated the effect of health-service interventions in bipolar disorder [31-35] and recurrent depressive disorder [36-41]. However, to the best of our knowledge, no randomised clinical trial has investigated the effects of centralised and specialised combined pharmacological and psychological intervention in the early phases of unipolar or bipolar disorders. There are indirect suggestions that early intervention may improve the course and outcome in affective disorders. As summarised by Berk et al. [42], lithium for instance may be less effective in bipolar disorder as well as in unipolar disorder if not initiated early [43-45] although not all studies confirm this finding [46,47]. Further, response to cognitive behavioural therapy (CBT, [48]) and to psychoeducation [49] may be more effective when used during the early course of illnesses than after a dozen illness episodes, although a meta-analysis showed no clear evidence that the numbers of episodes moderate the effect of psychological therapy [50]. In addition, brain imaging data suggest that cognitive decline and reduction in brain volume are linked to recurrences [51] and cognitive dysfunction may increase with increasing numbers of episodes [52]. Finally, lithium and other mood stabilizers may have protective effects decreasing the tendency to cognitive decline [53-57] but existing data does not lead to any definite conclusion of a neuroprotective effect of long-term lithium therapy. Similarly, data do suggest that maintenance antidepressants prescribed for unipolar depressive disorder may have neuroprotective abilities but this is not definitive either [58,59].

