### Randomisation

Patients were randomised to the intervention group or the control group at the end of the index hospitalisation. Randomisation was conducted centrally by the Copenhagen Trial Unit according to a computer generated allocation sequence to secure allocation concealment. In this way randomisation was independent of the professionals delivering treatment. The ratio of randomisation between the intervention and the control group was 1:1. Randomisation was stratified according to two variables: 1) psychiatric centres and 2) number of previous psychiatric hospitalisations (0, 1, or 2). The randomisations were carried out with varying block sizes unknown to the site investigators.

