### Sample size calculation

Anticipating a hazard ratio (HR) of 0.65 in the comparison of the intervention group with the control group on the primary outcome, a two-sided risk of type 1 error, α, of 0.05, a type 2 error risk, β, of 20%, and equal group size, the sample size (N) for trial I was calculated to N = 176 under the further assumption of a median time to re-hospitalisation of approximately 6 months in the control group, an inclusion period on 36 months, and a follow up period of 12 months. The sample size in trial II was based on similar assumptions (see Figure 1). However, patients with unipolar depressive disorder are more prevalent than patients with mania or bipolar disorder. Hence, we expected to be able to randomise more patients with unipolar depressive disorder. If we finally accrued a higher sample size in trial II compared to trial I, then the power for detection of a HR of 0.65 would become higher than 80%. The required sample sizes were calculated with the prospect of using a log rank test-statistic to test the null-hypothesis of no difference in time from randomisation to the primary outcome of re-admission to psychiatric hospital.

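### The primary log-rank test, as written, ignores the factors used to stratify randomisation; stratifying it by number of previous hospitalisations would protect power in trial I at little cost

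*Protocol article*

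**What the plan says.** Under Randomisation, the article states: "Randomisation was stratified according to two variables: 1) psychiatric centres and 2) number of previous psychiatric hospitalisations (0, 1, or 2". Under Statistical analyses, the primary comparison is described in one sentence: "The difference in cumulated prevalence of re-hospitalisation in the intervention and in the control group will be tested in log-rank tests". The same paragraph then adds a further analysis, in which "hazard ratios adjusted for age, sex, psychiatric centre, and number of previous admissions will be calculated in Cox' regression models". That model contains both stratification factors, but it is introduced as an addition to the test.

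The sections on sample size and on achieved power also rest on a log-rank statistic and mention no strata. The Background says that "the risk of relapse increases as the number of previous episodes increases". Trial I closed with 158 patients against a calculated 176, and the article states its power for a hazard ratio of 0.65 as 76%.

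**The concern.** Stratified randomisation makes the arms nearly equal in each stratum. If the strata carry different risks of re-admission, part of the chance variation that an unstratified log-rank test allows for has already been removed by design. The test then uses too large a variance, so its true type I error falls below 5%. In addition, when patients at different risk are pooled, the overall hazard ratio lies closer to 1 than the hazard ratio within strata. Both effects cost power.

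The article itself gives a reason to expect a gradient: it describes relapse risk as rising with previous episodes, and previous hospitalisations are a related count. Trial I is below its 80% target already, and the factor is known for every patient.

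**Working it through.** **Inputs from the article.** "a two-sided risk of type 1 error, α, of 0.05, a type 2 error risk, β, of 20%, and equal group size"; a hazard ratio of 0.65; a control median of 6 months; 12 months of follow-up after accrual of 36 months (Sample size calculation) or 48 months (Figure 1 legend, and the accrual actually used); 1:1 allocation; seven centres; three hospitalisation strata; 158 patients in trial I and 268 in trial II.

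**Assumed, because the article gives no figure.** How strongly the strata predict re-admission, and how patients are spread over them.

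**1. The stated power.** Freedman's formula with all 158 patients counted as events: sqrt(158) x (1 - 0.65)/(1 + 0.65) - 1.96 = 12.57 x 0.2121 - 1.96 = 0.706, which gives 76.0%, the article's figure. With censoring (48 + 12 months, exponential times, intervention hazard 0.65 times control) the mean event probability is 0.9227. That is 158 x 0.9227 = 145.8 events. Schoenfeld's formula then gives sqrt(145.8)/2 x |ln 0.65| - 1.96 = 6.037 x 0.4308 - 1.96 = 0.64, or 73.9%. Neither formula contains strata. The second is the baseline to expect in the simulations.

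**2. Stratifying by number of hospitalisations.** The unstratified statistic is U²/V, with U the sum of observed minus expected events in one arm. The stratified one is (sum of U_k)²/(sum of V_k), with U_k and V_k computed within stratum k. Simulation setting: 158 patients, allocation balanced within strata, uniform accrual over 48 months plus 12 months of follow-up, middle-stratum control median 6 months, hazard ratio 0.65 within each stratum, strata of equal size or 55/28/17%.

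| Stratum hazards (0/1/2 previous) | Unstratified power | Stratified power | Change, points |
|---|---|---|---|
| 1/1/1 | 73-74% | 71-72% | -1 to -2 |
| 0.75/1/1.33 | 71% | 71-72% | 0 to +1 |
| 0.6/1/1.6 | 64-65% | 68-71% | +4 to +6 |
| 0.5/1/2 | 57-59% | 67-70% | +9 to +13 |

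The true type I error of the unstratified test is about 4% in the third row and 3-4% in the fourth; that of the stratified test stays near 5%. Repeat simulations agree within 1 to 3 points. In trial II the two steeper rows give 86-87% against 90-91%, and 81-82% against 89-91%.

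**3. Which adjustment.** A second set of simulations for trial I (40,000 runs per scenario) used all 7 x 3 = 21 randomisation cells, blocks of 4 or 6, and a centre effect as well.

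| Hazard ratio per previous admission; centre SD | Unstratified | Stratified by admissions | Stratified by 21 cells | Adjusted Cox (Wald) |
|---|---|---|---|---|
| 1.0; 0 | 73% | 72% | 62% | 74% |
| 1.2; 0.1 | 72% | 71% | 62% | 74% |
| 1.3; 0.2 | 69% | 69% | 62% | 73% |
| 1.5; 0.3 | 63% | 66% | 62% | 73% |
| 2.0; 0.5 | 49% | 58% | 60% | 71% |

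The unstratified test's type I error runs 5.2, 5.0, 4.6, 4.0 and 2.8% down the rows. The Cox Wald test runs at 6.0-6.3%, so part of its apparent gain is excess false positives. The 21 cells hold 158/21 = 7.5 patients each on average, which explains the loss in that column. A ratio of 2.0 per admission is the 0.5/1/2 gradient, and the gain of about 9 points there matches the low end of the first table.

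**The case against.** **The article never says unstratified.** This stands as a limit. The word does not appear, and a fuller analysis plan could specify strata. Still, a log-rank test followed by adjusted hazard ratios as an addition reads most naturally as an unadjusted primary test.

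**Both factors are already in a planned analysis.** True. What remains is which analysis decides the primary question, and the test chosen matches the sample size calculation.

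**The gradient is invented.** The Background speaks of episodes, not hospitalisations, and gives no figure. The Limitations section says some patients had earlier, milder episodes that did not lead to admission, so the stratum is a diluted proxy. The steepest row gives patients with two previous hospitalisations four times the hazard of those with none, and nothing in the article supports that. This stands: the loss is conditional.

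**The simulations change the planned effect.** The plan's assumption is "Anticipating a hazard ratio (HR) of 0.65 in the comparison of the intervention group with the control group on the primary outcome", most naturally the overall hazard ratio. Setting 0.65 within strata weakens the overall value to about 0.67 and 0.70 under the two steeper gradients. With the overall value reset to about 0.65, unstratified power in trial I is roughly 71-74%. A reader might infer from the first table that the true power of trial I is 57% rather than 76%; the article does not support that. Stratification still gains several points after the reset.

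**The error is on the safe side.** This also stands. A reader might infer that the primary test is wrong or that a positive result would be in doubt. Neither follows, since type I error is at or below about 5%.

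**Conclusion.** The point holds as a conditional matter of efficiency. As written, the primary test leaves out the factors used in randomisation. If number of previous hospitalisations predicts re-admission, the test is conservative and trial I gives up power. The likely change from stratifying by that factor runs from a loss of 1-2 points if it has no prognostic value to a gain of 9-13 points under a steep gradient, for a hazard ratio of 0.65 within strata. Under a mild gradient it makes almost no difference. Where on this range the trials lie cannot be told from the article.

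It should be fixed because the possible gain is larger than the possible loss and the factor is already recorded. Two remedies that a reader might think equivalent are not. Stratifying on all 21 cells costs about 10 points when the strata are weakly prognostic. The adjusted Cox Wald test does not hold its 5% level in a trial of this size.

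**What to change.** Amend one sentence under Statistical analyses: the primary test in each trial is a log-rank test stratified by number of previous hospitalisations (0, 1, 2). State that the unstratified log-rank test, the Kaplan-Meier plot and the planned Cox hazard ratio adjusted for age, sex, centre and previous admissions are supportive. Do not stratify by all 21 cells. If the full analysis plan already specifies strata, say so in the article instead.

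The Blinding section places the analyses before unblinding, so the change should be dated before the re-admission data are analysed. It needs no new data. Its cost is 1-2 points of power in trial I if the factor proves not to be prognostic, and a primary test that no longer matches exactly the unstratified statistic behind the stated power.

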### Ethical considerations

The trials are approved by the Danish Research Ethical Committee (KF 01 272130) and the Danish Data Protection Agency (CVR-nr. 11-88-37-29). We have written informed consent from any patients involved in the trials, including consent to participate in the trials and consent to publish, where appropriate. Further, the trials are registered at http://www.clinicaltrials.gov (ID: NCT00253071). The trial participant's unique and personal identification number will be submitted to the Danish National Board of Health in order to link to data from the Danish Central Psychiatric Register, the Medicinal Product Statistics, and the Danish Medical Register on Vital Statistics to the study data.

## Results

### Current trial status

Recruitment of bipolar patients was somewhat slower than expected, so the recruitment period had to be extended one year further than the originally planned three-year inclusion period for both patient groups. Thus, patient enrolment started in December 2005 and closed in December 2009, resulting in enrolment and randomisation of a total of 426 participants, 158 with bipolar disorder and 268 with unipolar disorder. Accordingly, we did not reach the planned number of 176 patients with bipolar affective disorder. Among unipolar patients, 63.1% were women and the median age was 38.6 years (quartiles: 31.1 to 53.4). Among bipolar patients, 54.4% were women and the median age was 35.6 years (quartiles: 27.7 to 47.1).

### Power calculations for trials I and II

In the bipolar disorder trial I, the number of 158 recruited patients results in a power of 76% (power = 1-β) for the detection or rejection of a HR of 0.65. In the unipolar disorder trial II, the number of 268 recruited patients results in a power of 93% for the detection or rejection of a HR of 0.65. The power in trial I would be 60% and the power in trial II 82% to detect or reject a HR of 0.70. The power in trial I would be 42% and the power in trial II 63% to detect or reject a HR of 0.75. The statistical power in the two trials is calculated with the prospect of using a log rank test-statistic to test the null-hypothesis of no difference in time from randomisation to the primary outcome.

## Discussion

### Limitations

It is an inherent limitation of the trials designs that it is not possible to blind patients and treating clinicians for intervention due to the nature of the intervention (specialised out-patient intervention versus standard treatment). This may limit the inferences based on these trials. The trials aim to investigate the effect of specialised and centralised secondary care intervention early in the course of severe affective disorders, i.e., in patients discharged from their first, second, or third hospitalisation. It is evident that some of these patients may have experienced prior affective episodes less severe than those resulting in hospitalisation and there may have been a delay in seeking help and diagnosis of the mood disorder [45,46] as reflected in the relatively high median age (especially for bipolar patients). Nevertheless, randomisation should take care of this potential confounder in our analyses.

Further, it should be noted that the study is estimating the effect of a complex intervention in a centralised and specialised mood disorder clinic. The intervention consists of a combination of many different elements and we suspect it will be impossible to differentiate the effect of the different intervention components consisting of medical treatments, psychoeducation, cognitive behavioural intervention, and social support.

The patients in the experimental intervention group received a well-defined intervention program according to a manual. Little is known about the treatment offered to the patients in the control group. It is likely that the patients in the control group received very different intervention offers and that these interventions varied between a broad, competent and prolonged service to a much shorter and sporadic offer of treatment. Furthermore, the intervention in the control group may change over time to become similar to the intervention in the experimental group because of increased focus on treatment of affective disorders (possibly also due to the Danish HTA report [63]), the growing evidence of the effect of combined intervention (pharmacologically and psychologically) and because of a rub-off effect from the many leading local clinicians involved in the allocation of patients to the trials.

Even though there were very few exclusion criteria, it is likely that patients who accept randomisation may be a selected group and that patients with the most severe illness, with comorbidity, e.g., substance abuse are under-represented. Furthermore, the current design may introduce attrition bias as the more severely ill and patients with comorbid substance use problems and other comorbidity may be more able and willing to attend locally tailored treatment rather than centralised treatment. Participants and eligible non-participants will be compared using register-based variables to evaluate whether participants in the trials are representative of patients with affective disorders, discharged form their first, second or third hospitalisation.

### Advantages

Central randomisation protect against selection bias in the randomisation process. Further, it is a major advantage that the primary outcome measure, i.e., first re-admission to a psychiatric ward can be obtained for all included patients in the trials based on data from a nation-wide health register data [72]. Data on outpatient pharmacological treatment will be obtained from the Medicinal Product Statistics that contains data on all prescribed medication purchased nationwide at pharmacies from January 1, 1995 and onwards [87].

#### Generalisability

Pragmatic trials as the present trials are designed to measure effectiveness; that is whether an intervention works when used in usual conditions of care. To ensure applicability in a wide range of usual care settings, pragmatic trials should include all kinds of participants to whom the intervention may be offered in the real world, if its effectiveness is established [62]. A total of seven psychiatric centres participated in our trials out of the 9 centres that offer acute hospitalisation in The Capital Region of Denmark. The two non-participating centres do not differ noticeably in patient population of affective disorders or treatment services from the seven centres. The trials include a moderately large number of patients and have a naturalistic design with inclusion of patients suffering from severe affective disorders with all kinds of symptoms and comorbidities and with very few exclusion criteria. Thus, patients with depressive, manic or mixed index episodes, early and late onset, with or without psychosis and comorbidity, such as personality disorders, alcohol or substance abuse, etc, as well as patients with poor or good treatment outcome during hospitalisation were included. It should be noted that participants were included in the trials based on the diagnoses established by the treating medical doctors employed at the psychiatric hospitals to obtain a high generalisability of results from the trials to clinical settings regarding patients with the most severe affective disorders. Including only patients who fulfil diagnostic criteria for an affective disorder according to a research-based interview (such as, e.g., the SCAN interview) in the trials would not mimic the naturalistic clinical setting to which we wanted the results to be generalisable. Nevertheless, the validity of diagnoses made by physicians at discharge from psychiatric hospitals in Denmark is reasonably high compared to research-based diagnostic interviews with a probability of a correct diagnosis for bipolar disorder of 94% [88] and with a probability of a correct diagnosis for unipolar disorder of 83% [89].

Hospitalisation as an outcome has been criticised as reductionistic. However, it benefits from being consistently recorded and has high face validity as admission to hospital reflects a serious relapse of the illness [90]. Nevertheless, it is possible that the decision to admit a patient in our trials were influenced by the treating physicians' attitude toward centralised and specialised treatment although it is not evident that such attitudes may cause bias. In the experimental group, physicians in the mood disorder clinic may be reluctant to admit a patient in order to increase the apparent benefits of the mood disorder clinic or, in contrast, admit the patient earlier and more often as these are followed more closely, which will make the experimental intervention look worse. In the control group, the physicians may be eager to admit a patient to prove the advantages of the mood disorder clinic or, in contrast, be reluctant to admit the patient to prove the benefits of standard care. We are able to estimate the effect of such potential bias by comparing diagnoses on severity of the illness leading to hospitalisation (current depressive episode mild, moderate or severe, current episode hypomanic or manic; with or without psychotic symptoms) given by the inpatient physicians at discharge from the outcome hospitalisation for the intervention and the control groups, as these are recorded in the Danish Psychiatric Central Register. The physicians at the psychiatric centre give diagnoses independently of the referring outpatient physician. In addition, it is not clear that the potential effect of such attitudes differs in the experimental trial setting and the non-experimental everyday clinic. It should be realised that the rate of (re-) hospitalisation in the trials should be considered in relation to other outcome measures such as the proportion with relapse and suicide in the two groups of the trials. Notably, researchers did not assess patients during the follow-up as the primary outcome as well as one tertiary (suicide) outcome was based on register data and other outcomes were based on a questionnaire mailed to the participants. Using this simple approach, the research team did not interact with the patients in the trials in any way, i.e., the research team had no effect on inclusion of participants into the trials, delivered treatment or drop-out from treatment, in contrast to what is the case in trials with extensive and repeated assessment by researchers. Our trials are thus designed to closely imitate the clinical situation and results from the trials may be generalised to patients discharged from early admissions with a manic episode/bipolar disorder or a single moderate to severe depressive episode or recurrent depressive disorder, respectively, and the results should be generalisable into the everyday clinic.

The downside of this simple approach is that the secondary and most tertiary outcomes are based on patient's self-assessment that may have a decreased validity, especially during manic episodes. We used the Mood Disorder Questionnaire (MDQ) to assess the development of a manic/mixed episode of at least moderate severity although it is critical whether this is a reliable approach.

The health care system in The Capital Region of Copenhagen is similar to the health care system elsewhere in Denmark and to the majorities of Western countries with a large primary health care system of general practitioners and private specialists and a smaller secondary health care sector including hospitals and community psychiatric centres. Thus, we believe that the results of the trials should be generalisable to most Western communities.

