### Blinding

Blinding of patients and the treating clinicians was not possible as patients were randomised to the mood disorder clinic or to standard treatment. Nevertheless, statistical analyses and the writing of the scientific paper including introduction and results will be carried out before data are unblinded.

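### Comparing severity diagnoses among re-admitted patients cannot estimate biased admission decisions, as the article says it can

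*Protocol article*

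**What the plan says.** Under Outcome assessments, the primary outcome of both trials is time from randomisation to first psychiatric re-admission with an affective episode. Under Blinding: "Blinding of patients and the treating clinicians was not possible".

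The Generalisability section raises this concern: "the decision to admit a patient in our trials were influenced by the treating physicians' attitude toward centralised and specialised treatment". It lets this run in either direction and in either arm. One case in the experimental arm is that "physicians in the mood disorder clinic may be reluctant to admit a patient in order to increase the apparent benefits of the mood disorder clinic". The opposite case is that they "admit the patient earlier and more often as these are followed more closely, which will make the experimental intervention look worse".

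The answer given is "We are able to estimate the effect of such potential bias by comparing diagnoses on severity of the illness leading to hospitalisation". The diagnoses meant are those "given by the inpatient physicians at discharge from the outcome hospitalisation for the intervention and the control groups"; they are held in the national psychiatric register. Two supports follow. The first is that "The physicians at the psychiatric centre give diagnoses independently of the referring outpatient physician". The second is that the re-hospitalisation rate "should be considered in relation to other outcome measures such as the proportion with relapse and suicide in the two groups of the trials".

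No assumption is attached to the claim. The comparison is not listed under Statistical analyses.

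**The concern.** A discharge diagnosis from the outcome hospitalisation exists only if there was an outcome hospitalisation. Re-admitted patients in the two arms are not a randomised comparison. The treatment determines who relapses and how badly, and the admission decision, which is the very thing under suspicion, determines who then enters the comparison.

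The check could therefore mislead in both directions. If the programme prevents milder relapses more than severe ones, its re-admissions look more severe although nobody has changed the threshold for admission. If clinic doctors hold back patients at every severity to the same degree, the severity mix is unchanged and the check shows nothing.

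This is the only method the article says can estimate the bias, and the outcome it is meant to protect is the primary outcome of two open-label trials. A reader of the results could be told that the bias had been measured when it had not.

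**Working it through.** The article gives no figure for this check, so there is nothing to reproduce. The question is whether the stated comparison can identify the bias.

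**Model.** For severity k, let r be the relapse rate and a the probability that such a relapse leads to admission. Then

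re-admission rate at k = r(k) × a(k).

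The register shows this product and neither factor.

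**Inputs.** The anticipated hazard ratio of 0.65 is from Sample size calculation. All relapse rates and admission probabilities below are assumptions, chosen only to show what is possible, because the article gives none. Relapses are per 100 in control, ordered mild / moderate / severe.

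| Scenario | Relapses | Admission probability | Re-admissions | Total | Severity mix |
|---|---|---|---|---|---|
| Control | 30/40/30 | 0.5/0.8/1.0 | 15/32/30 | 77 | 19.5/41.6/39.0% |
| A: bias only | 30/40/30 | 0.2/0.6/1.0 | 6/24/30 | 60 | 10/40/50% |
| B: real effect only | 12/30/30 | 0.5/0.8/1.0 | 6/24/30 | 60 | 10/40/50% |
| C: bias only, all admission probabilities × 0.65 | 30/40/30 | 0.325/0.52/0.65 | 9.75/20.8/19.5 | 50.05 | 19.5/41.6/39.0% |
| D: real effect only, all relapses × 0.65 | 19.5/26/19.5 | 0.5/0.8/1.0 | 9.75/20.8/19.5 | 50.05 | 19.5/41.6/39.0% |

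**A against B.** The severe share is 50% against 39% in control in both, and the counts agree as well as the percentages. In A nothing was prevented. In B nobody's threshold changed. A severity difference therefore does not show bias.

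**C against D.** These too are identical, and both have exactly the control arm's severity mix. The ratio of totals is 50.05/77 = 0.65. Read as rates, with a relapse that is not admitted leaving the patient at risk as before, the hazard ratio is Σ r(k) × 0.65 × a(k) / Σ r(k) × a(k) = 0.65. Equal severity is therefore compatible with the whole anticipated effect being due to reluctance to admit.

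**Generality.** Take any bias-only pattern with changed admission probabilities a′(k). An effect-only pattern with relapse rates r(k) × a′(k)/a(k) and unchanged admission, where a(k) > 0, gives the same re-admission rates. When a′(k) ≤ a(k), this needs only a reduction in relapses.

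**The missing assumption.** To read a severity difference as bias, one must assume that treatment leaves the severity mix of relapses unchanged. The Hypotheses section expects fewer relapses, and the Intervention group section describes training patients to recognise early warning signs, so a changed mix is plausible without bias. Even when the assumption holds, as it does in C, the comparison can detect only bias that varies with severity.

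**The case against.** The strongest reply is that this is a Discussion remark under Generalisability. It sets no endpoint, does not appear under Statistical analyses and cannot change the primary result. The same section doubts that such attitudes cause bias, and doubts that their effect differs from everyday care, which matters in a pragmatic trial. That limits the point to an overstated inference. It does not make the inference correct, because the sentence names a concrete comparison and says without condition what it will deliver.

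A second reply is that the article does not confine itself to percentages among the re-admitted. Register data cover everyone randomised, so severity-specific counts per arm are available. This is so, and the fix uses it. But A and B, and C and D, agree on counts too.

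A reader might infer that this check is the plan's only protection. The article does not support that. It also cites the independence of ward diagnoses and the reading of relapse and suicide alongside, and Perspectives asks for caution because of the lack of blinding. These supports do not supply the missing estimate, however. Independence from the referring doctor is not described as blinding to arm, and it does not undo selection into admission. Relapse is self-reported by mailed questionnaire from unblinded patients, with some data missing, and the article itself doubts this measure in mania. Suicide does not show which relapses led to admission. Having analysis and writing done before unblinding does not touch admission decisions.

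The figures are wholly assumed. They show what is possible and give no likely size.

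**Conclusion.** The claim that the effect of admission bias can be estimated this way is wrong as written. Without the assumption of an unchanged severity mix, a difference between arms does not show bias. With or without that assumption, equal severity does not exclude it. In the illustration, bias of a size that alone gives a hazard ratio of 0.65 leaves the severity mix unchanged at 19.5/41.6/39.0%. The identifiability argument rests on no figure in the article. The numerical scenarios rest on assumed relapse rates and admission probabilities.

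The comparison still has descriptive value as a signal that thresholds may differ. The point does not show that admissions in these trials were biased, nor that the primary log-rank analysis is incorrect, and the article supports neither inference. It changes what may be concluded about the open-label primary outcome.

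**What to change.** Replace the statement that the bias can be estimated with one that the severity comparison among re-admitted patients is descriptive. Say that reading a difference as bias assumes treatment leaves the severity mix of relapses unchanged, and that equal severity does not rule bias out.

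Add a supportive analysis in all randomised patients of each trial:

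- Time from randomisation to first re-admission with a severe or psychotic affective episode, using the planned log-rank test and Cox model. Fix in advance, separately for trials I and II, which register diagnoses count, because the severity categories the article lists differ for depression and mania.
- Cause-specific hazard ratios for milder and for severe re-admissions.
- 95% confidence intervals for each.

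Treat agreement between the severe-episode and primary results as supportive only, with no pass/fail robustness rule. In scenario C the severe-episode ratio is 19.5/30 = 0.65 with no treatment effect, so such a rule would clear a fully biased result.

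The cost is a revised sentence and some extra analysis on register diagnoses the article already names. The severe-episode analysis will have fewer events and wider intervals, and its diagnoses still come from wards not described as blinded to arm.
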